### Statistical analyses

#### Primary and secondary outcomes

Data will be analysed using intention-to-treat principles. Once a participant is randomised into a study group, they will be considered a trial participant and analysed according to their allocated group, regardless of missing data for follow-ups or the amount of intervention received. Each primary and secondary outcome will be modelled using mixed linear models with random intercepts, the fixed effects of study group, time and a group by time interaction as well as baseline values (to account for regression to the mean). Potential confounders include baseline characteristics and the factors used to balance groups by minimisation. Confounders will be identified by forwards and backwards selection. Inclusion in the final model will require the addition or omission of the potential confounder to elicit a substantial change in the coefficient for the effect of intervention. A 20% change in coefficient will be considered substantial unless the coefficient is close to zero. Data analysis will be performed using [SAS/STAT] software, Version [9.2] of the SAS system for Windows. Statistical significance will be set at the conventional two-tailed 5% level.

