### Purpose

This paper describes the methods of the Living Well with Diabetes trial which is evaluating a telephone-delivered behavioural weight loss intervention focussing on physical activity, diet and behavioural therapy in adults with type 2 diabetes. To promote maintenance the 18 month intervention has an intensive first 6 months focussed on *initiation *of behaviour change, followed by 12 months focussed on enhancing/supporting *maintenance*. Measurement at baseline, six, 12, 18, and 24 months allows for assessment of *initiation *and *maintenance *of change - a major contribution of the study to the evidence base on broad reach interventions to support weight loss and lifestyle management in type 2 diabetes.

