### Primary and secondary outcomes

Primary outcomes are: change in weight (kg), accelerometer-measured moderate-to-vigorous physical activity and glycaemic control (HbA1c). Secondary outcomes are: change in self-reported dietary and energy intake, accelerometer-measured light intensity and sedentary time, objectively measured waist circumference, percent body fat, fasting plasma glucose and blood lipids (total cholesterol, HDL-cholesterol, LDL-cholesterol, triglycerides), liver function enzymes, blood pressure, along with self-reported SCE constructs, medication use and health-related quality of life. We will also evaluate the incremental cost-effectiveness of the telephone intervention and examine demographic and health-related moderators of intervention effects and mediators consistent with the underlying theoretical basis. Related measures are described below and summarised in Table 3.

**Table 3 T3:** Summary of Measures

**Anthropometric**	**#**Weight****
	#Waist circumference
	% body fat
	
Cardio-metabolic	**Glycoslyated haemoglobin**
	Fasting blood glucose
	Cholesterol (total, HDL, LDL)
	Triglycerides
	Liver function tests (ALT, AST, LDH, ALP, GGT)
	Blood pressure
	Diabetes medication
	
Behavioural	#**Objectively measured physical activity (PA) via accelerometer**
	Average mod-vig PA/day (mins)
	Average light intensity PA/day (mins)
	Average very light intensity PA/day (mins)
	Average sedentary time/day (mins)
	Breaks in sedentary time (n/day)
	Bouts of moderate-to-vigorous intensity activity (n/day)
	Self-reported physical activity
	Walking (days & min/wk)
	Walking for exercise (days & min/wk)
	Moderate-vigorous PA (days & min/wk)
	Resistance training (days & min/wk)
	Sitting items (transport, television, computer min/wk)
	Self-reported diet
	Dietary intake (total energy, total fat, saturated fat, fibre)
	Dietary behaviour
	Sleep (duration & quality)
	
Psychosocial-Environmental	Depression
	Self-efficacy
	Social support
	Perceptions of the neighbourhood environment
	
Cost-effectiveness	Health-related quality of life
	Health care utilization
	Cost to deliver intervention
	
Intervention Delivery (tracked for each call)	Call duration
	Call completion

All assessed at baseline, 6, 18 & 24 months; #assessed at 12 months; bold text denotes primary outcome

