### Data collection

Data are collected via objective measurements conducted in participants' homes, telephone interviews, and self-administered questionnaires at baseline, 6-, 18-, and 24-months by research staff and registered nurses blind to participants' study group. At 12 months, weight, waist circumference and accelerometer-derived physical activity are also assessed. Home visits are conducted by registered nurses and include objective measurement of: height (baseline only; Seca 214 height rod, Seca, Germany), weight, waist circumference, body composition, blood pressure and collection of blood samples for biochemical assay. In addition, details of diabetes medications (drug and dosage) and any use (yes/no) of antihypertensive and lipid-lowering medications are also collected during this visit. Telephone interviews collect self-report data on: demographics (gender, age, education, income, type and number of chronic conditions; baseline only), and validated measures of physical activity, diet, quality of life and health care use, as well as items to assess sleep, diabetes history and management, use of weight loss aids and adverse outcomes. Self-administered questionnaires are used to collect data related to the social-cognitive and environmental constructs which underpin the intervention and to assess depression. In addition to the self-reported physical activity collected via the telephone interviews, accelerometers are used to collect objectively-measured physical activity and sedentary time. Data related to intervention delivery are also tracked by telephone counsellors following each call. This includes data on call outcomes (call completion versus missed calls), call duration and call content (via a checklist of topics). Details of the measures are provided below and summarised in Table 3.

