### Sample size

Effect size estimates for the proposed study take into account clinically meaningful differences and are based on published results [24,111,112], and unpublished data from our recent trials. The minimum differences of interest in change from baseline to 18-months follow-up between intervention and usual care groups for our primary outcomes are: -5% of initial body weight; +60 minutes/week for moderate physical activity; -0.6% for HbA1c. Sample size estimates are based on the expected mean difference for physical activity, as this variable required the largest sample size. To detect a mean difference of 60 minutes per week change in accelerometer-derived moderate-to-vigorous intensity physical activity between the intervention and control groups with 90% power and 5% significance (two-tailed), assuming a standard deviation of 140 minutes (based on unpublished data), requires 115 subjects per group. Assuming an attrition rate of 30% means that 150 participants per group are required (300 participants overall). This sample size provides sufficient power (80% or more) to detect the following intervention effects for sedentary time (-45 minutes/day); light intensity time (+30 minutes/day); and, our secondary outcomes: -2,000 kJ for energy intake; -5% for energy from fat; -2% for energy from saturated fat; -5 to 10% for cholesterol (total, LDL-, HDL-); -15% for triglycerides; -1 mmol/L for fasting plasma glucose; -5 mmHg for systolic blood pressure; -5 cm for waist circumference; and, -2% for body fat.

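### As written, the random-intercept model gives every follow-up visit the same variance and correlation; if the spread of outcomes changes over time, the visit-specific standard errors are wrong, most of all at 24 months

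*Protocol article*

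**What the plan says.** The protocol article fixes one model for all outcomes under Statistical analyses, Primary and secondary outcomes. Each is to be "modelled using mixed linear models with random intercepts, the fixed effects of study group, time and a group by time interaction", and the model also contains the outcome's own baseline: "as well as baseline values (to account for regression to the mean". Baseline is therefore a covariate, and the repeated responses are the follow-up visits. The section mentions no random slope, residual covariance structure or robust standard error, and it rules none of them out. On testing it says: "Statistical significance will be set at the conventional two-tailed 5% level".

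The number of follow-up visits depends on the outcome. The footnote to Table 3 reads "All assessed at baseline, 6, 18 & 24 months; #assessed at 12 months; bold text denotes primary outcome", and the Data collection section adds: "At 12 months, weight, waist circumference and accelerometer-derived physical activity are also assessed". Weight, waist and accelerometer outcomes thus have four follow-ups (6, 12, 18 and 24 months). HbA1c and most other outcomes have three (6, 18 and 24 months).

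Two late visits carry particular weight. The Sample size section defines "The minimum differences of interest in change from baseline to 18-months follow-up between intervention and usual care groups", so 18 months is the visit to which the target differences refer. The Discussion part of the abstract presents the 24-month assessment, six months after the intervention ends, as a main contribution.

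**The concern.** A random intercept for each participant with ordinary independent residuals implies the same total variance at every visit and the same correlation between every pair of visits. The group difference at each visit is then given a standard error built from one pooled variance. If the true spread around the baseline-adjusted mean differs by visit, the pooled figure is too large where spread is small and too small where it is large.

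The design gives no reason to take equal spread for granted. Visits lie 6 to 24 months from the baseline value used for adjustment. Contact falls from weekly to fortnightly to monthly and stops at 18 months. The Phase 3 text expects some participants to be still working towards their targets while others maintain them. For HbA1c the gaps between follow-ups are 12 and 6 months, yet the model gives both the same correlation. None of this shows that spread grows. It shows that the model rests on a condition the article does not support.

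If spread does grow, the contrast most exposed is the 24-month one, which carries the claim about maintenance. Its intervals would be too short and its test would reject too often.

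**Working it through.** **The plan's own figure.** Inputs from the Sample size section: difference 60 min/week, SD 140, 90% power, two-sided 5%.

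n per group = 2 × (1.960 + 1.282)² × (140/60)² = 2 × 10.51 × 5.444 = 114.4, which rounds up to the stated 115. The 140 is the only SD given, and there is none by visit.

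**Complete data.** With a separate group effect at each visit, the compound-symmetry fit pools the visit variances, so at visit t

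model SE / true SE = √(mean of the visit variances / variance at t)

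and the true level of the nominal 5% test is 2 × [1 − Φ(1.96 × ratio)].

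Assumed: the SD grows linearly from 6 to 24 months by a factor of 1.25, 1.5 or 2.0. Worked for a factor of 1.5 and four visits:

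- SDs 1, 1.167, 1.333, 1.5; variances 1, 1.361, 1.778, 2.25; mean 1.597; root 1.264.
- Ratios 1.264/1 = 1.26, 1.264/1.167 = 1.08, 1.264/1.333 = 0.95, 1.264/1.5 = 0.84.
- Type I error 1.3%, 3.4%, 6.3%, 9.9%.

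On the plan's scale (average SD 140, 115 per arm) the model gives a 95% half-width of 1.96 × 140 × √(2/115) = 36.2 min/week at every visit. The correct half-widths in this scenario are 28.6, 33.4, 38.2 and 42.9.

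**With dropout.** Assumed: loss completely at random, building up linearly to the planned 30% by 24 months; true correlation either 0.8 per six months (decaying) or 0.6 throughout. The limiting compound-symmetry fit was found and its model-based SE compared with the sandwich SE. Type I error for four visits (ranges span the two correlation patterns):

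| SD growth, 6 to 24 months | 6 m | 12 m | 18 m | 24 m |
|---|---|---|---|---|
| ×1.0 | 5.0% | 4.9-5.0% | 5.0-5.1% | 5.0-5.6% |
| ×1.25 | 2.9% | 4.3-4.4% | 6.1-6.2% | 8.0-8.7% |
| ×1.5 | 1.5-1.6% | 3.7-3.8% | 6.9-7.0% | 10.6-11.3% |
| ×2.0 | 0.3-0.4% | 2.8% | 7.9-8.0% | 14.4-15.1% |

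For HbA1c (three visits) with the same dropout, the three growth factors give 5.8-5.9%, 6.4-6.5% and 6.8-7.0% at 18 months, and 7.7-8.1%, 9.9-10.3% and 13.0-13.4% at 24 months.

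**Other patterns, four visits, complete data.**

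- Late growth (SDs 1, 1.05, 1.15, 1.5): mean variance 1.419, root 1.191. The ratio is 1.191/1.15 = 1.04 at 18 months (slightly too wide) and 1.191/1.5 = 0.79 at 24 months. With dropout and decaying correlation these become 1.01 and 0.76.
- Shrinking spread (1.5 down to 1.0, linear): the ratio is 1.264/1.167 = 1.08 at 18 months and 1.264/1 = 1.26 at 24 months, both too wide.
- Constant spread with decaying correlation: the ratio is 1.00 at every visit. With 30% dropout it is 0.97 at 24 months, the 5.6% in the table. Unequal correlation alone therefore matters little.

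**The case against.** The strongest objection is that the text does not say random intercepts only. A random intercept can sit alongside heterogeneous residual variances or empirical standard errors, and a journal article may leave such detail to an analysis plan that is not shown. A reader might infer that the plan has ruled these out; the article does not support that. What remains is that the article does commit to a covariance model for every outcome, and that model, followed as written, is compound symmetry. The point is to improve a stated choice, not to supply an omitted detail.

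The second objection is that growing spread is assumed. This is correct: the article gives one SD, for physical activity, and says nothing about spread by visit. A reader might infer that the late contrasts will be tested above their nominal level. The documents do not show that; it follows only if spread grows.

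The third is that the effect is weakest at 18 months, where the target differences are set. This also stands. Under steady growth the 18-month standard error is short by only 2-7% with complete data and by 4-11% with dropout, and under late or shrinking patterns the error changes direction. A general statement that the 18-month intervals are too narrow would be wrong.

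A reader might also infer that the misfit biases the estimates through the way missing visits are implicitly predicted. No bias was estimated, and the 30% is a planning allowance, so no size can be put on it.

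**Conclusion.** The point holds as a conditional weakness of a stated model, not as a demonstrated error. Reading the intercept as the participant's, with ordinary residuals, the model's visit-specific standard errors are right only if the baseline-adjusted spread is constant over follow-up.

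If the SD grows steadily by ×1.25 to ×2.0 and 30% drop out, the 24-month intervals are clearly too narrow (type I error about 8-15%), the 18-month intervals slightly so (about 6-8%), and the 6-month intervals too wide. For HbA1c, with three follow-ups, the figures are a little smaller. If spread is constant, the level is about 5-5.6% and nothing is lost. These sizes rest on the assumed SD patterns, the two assumed correlation patterns and dropout completely at random.

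The case for changing the model does not depend on which pattern is true. An unstructured covariance gives valid large-sample standard errors whether spread grows, shrinks or stays the same.

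**What to change.** Replace the random intercept by an unstructured covariance over the follow-up visits: in PROC MIXED, REPEATED visit / SUBJECT=id TYPE=UN, with Kenward-Roger degrees of freedom. State the visits per outcome: four for weight, waist and accelerometer measures, three for HbA1c and most others.

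Name the fallback in advance. If the model does not converge, use a structure with a separate variance for each visit, or keep the random intercept with empirical (sandwich) standard errors. The sandwich repairs the standard errors but leaves the implicit prediction of missing visits as it was, so it is the weaker fallback.

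The cost is 10 covariance parameters with four visits (4 variances and 6 covariances), or 6 with three, instead of 2. That is modest with 300 participants, and the change is small in the SAS software the plan already names. A baseline-by-visit interaction may be added, but this defect does not require it. The choice should be fixed before outcome data are seen by group.

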### Randomisation

Following baseline data collection, allocation to study groups (telephone intervention or usual care) is conducted using the method of minimization to ensure equal group balance across factors likely to impact on primary study outcomes [45,46]. Minimisation factors based on baseline data collection include: gender, age (< 55 years; ≥ 55 years), BMI (< 40 kg/m^2^; ≥ 40 kg/m^2^), HbA1c (< 8%; ≥ 8%), physical activity level (meeting guidelines of at least 150 minutes/week and 5 or more sessions; not meeting guidelines) [47], and diabetes management (insulin or combination therapy; traditional oral hypoglycaemic medications; new glucose-lowering medications (e.g. Byetta, Januvia); lifestyle alone). Allocation is performed using the free Minim computer software [48] and conducted by a research assistant with minor involvement in participant recruitment. The timeframe from participant recruitment to group allocation ranges from approximately three to eight weeks to allow for extensive baseline data collection (see Data Collection section below), and not all minimisation factors are known at recruitment (e.g. HbA1c level, diabetes management). Therefore, the ability for the staff member to predict with certainty, the allocation of participants at recruitment, a criticism of the minimisation method [46], is near impossible.

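### The 20% change-in-coefficient rule almost never keeps the minimisation factors at the planned effect and lets the observed effect decide the adjustment set; the cost is precision, not validity

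*Protocol article*

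**What the plan says.** Under Randomisation, the protocol article states that allocation is done "using the method of minimization to ensure equal group balance across factors likely to impact on primary study outcomes". There are six factors: gender, age, BMI, HbA1c and physical activity level, each in two categories, and diabetes management in four.

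Under Statistical analyses (Primary and secondary outcomes), each outcome has a mixed linear model with random intercepts. The terms always present are group, time, group by time and baseline values. Everything else is optional: "Potential confounders include baseline characteristics and the factors used to balance groups by minimisation". The procedure is "Confounders will be identified by forwards and backwards selection", and the criterion is "Inclusion in the final model will require the addition or omission of the potential confounder to elicit a substantial change in the coefficient" for the intervention effect. The threshold is then given: "A 20% change in coefficient will be considered substantial unless the coefficient is close to zero".

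Nothing in the article forces the minimisation factors into any model or names a fixed covariate set.

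**The concern.** A change-in-estimate rule is a tool for confounding in observational data. In a linear model, a covariate moves the treatment coefficient through imbalance between the arms, and minimisation exists to remove that imbalance. The rule therefore tests the six factors for the property that the design has suppressed. It ignores their prognostic value, which is the reason to adjust for them in a randomised trial. Allocation that uses the factors, followed by analysis that omits them, leaves their variance in the residual. The reported standard error then tends to exceed the true variability of the estimate.

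The threshold is also relative to the estimate itself. The same small imbalance fails the rule when the observed effect is large and passes it when the observed effect is small. The covariate set thus follows from the result, separately for each outcome. At stake are precision and a primary model that can be stated before the data are seen.

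**Working it through.** **Inputs from the article (Sample size; Randomisation).** Difference 60 min/week, SD 140, two-sided 5%, 90% power, 115 per group, 30% attrition, 150 per group randomised, six minimisation factors.

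**Step 1: the plan's own figure.** n = 2 × (1.960 + 1.282)² × (140/60)² = 114.4, so 115 per group. This reproduces. With 30% loss, 150 per group leaves 105. The unadjusted standard error is then 140 × √(2/105) = 19.3, and power is Φ(60/19.3 − 1.96) = 87%.

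**Step 2: what a factor needs in order to enter at the planned effect.** Suppose the six factors together explain a share R² of the variance left after the baseline outcome, equally divided (an assumption; the article gives no R²). One standardised binary factor then has coefficient 140 × √(R²/6), and adding it shifts the treatment coefficient by about that coefficient times the imbalance in SD units.
- The 20% threshold at an observed effect of 60 is 12 min/week.
- At R² = 10% the coefficient is 18.1, so the imbalance needed is 12/18.1 = 0.66 SD.
- At R² = 30% the coefficient is 31.3, so the imbalance needed is 12/31.3 = 0.38 SD.
- If minimisation leaves near-perfect balance at allocation, the imbalance arising from random 30% dropout has SD of about √(2 × 0.3/105) = 0.076.

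The required imbalance is therefore about 5 to 9 times what is likely to occur. If the observed effect happens to be 5 min/week, the threshold falls to 1 min/week. The imbalance needed at R² = 10% is then 1/18.1 = 0.055 SD, which chance supplies readily.

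**Step 3: simulation.** Four sets of runs (600, 800, 1,000 and 2,500 trials per setting) used 300 participants, deterministic minimisation on six factors, 30% random dropout and forward-then-backward selection at 20%. Factor prevalences, R² and the number of other baseline covariates are assumptions. The 800-trial set analysed a single follow-up, did not model the baseline outcome separately and applied no near-zero exception, because the article gives no value for one.

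| True effect (min/week) | Trials retaining at least one minimisation factor |
|---|---|
| 60 (planned) | about 0.5-2% |
| 30 | 14-29% |
| 0 | 34-73% |

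| Assumed R² | Power at 60, 20% rule | Power at 60, factors fixed |
|---|---|---|
| 5% | 86-87% | 87-88% |
| 10% | 87-90% | 89-91% |
| 20% | 88-89% | 93-94% |
| 30% | 88-89% | 95-96% |

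Ranges are across sets of runs; within a set the loss was about 1 point at 5%, 1-2 points at 10%, 5 points at 20% and 6-7 points at 30%.

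**Step 4: standard error, type I error, bias under the rule.**
- *Reported mean SE against the empirical SD at the planned effect.* At R² = 10%, 19.4 against 18.1 and 19.3 against 18.5 (4-7% too large), but in another set 0.138 against 0.137 in SD units (under 1%). At 20%, 19.3 against 17.7 (9%). At 30%, 19.3 against 17.2-17.4 (11-12%).
- *Type I error.* 4.6-5.5% at R² = 10%, 3.4% at 20% and 2.4-3.1% at 30%. In the 800-trial set the Monte Carlo standard error is about 0.8 points.
- *Bias.* Mean estimates under the rule stayed within 0.5 min/week of those from the fixed model in every setting of the 800-trial set.

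**The case against.** The strongest reply is that the loss is small and falls on the safe side. Baseline values are always in the model. For HbA1c, the corresponding minimisation factor is a category of that baseline; for weight and activity, the BMI and activity-level factors overlap heavily with it. Only what the remaining factors add counts, and at 5-10% that is 1-2 power points. This stands, and it limits the size of the point. It does not justify a rule that excludes allocation factors because they are balanced.

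Several stronger readings are tempting but not supported:

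- *That the rule always drops the minimisation factors.* This is nearly true at the planned effect only. With a small or null effect, chance brings some in.
- *That the intervals and p-values of all three primary outcomes are invalid.* The simulations show a near-nominal or conservative test and no noticeable bias. The rule was not seen to raise the rate of false claims of benefit.
- *That standard errors are too large by the full 1/√(1 − R²)*, that is 3% at R² = 5% up to 20% at R² = 30%. That formula assumes perfect balance in the analysed set and no factor ever entering. Dropout weakens the first, and the second fails under the null. R² must also be read as what remains after the baseline outcome.
- *That an analyst with knowledge of the arms would choose the covariates.* The article does not say so, and the rule could be run on coded groups. The choice would still depend on the estimate.

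The meaning of a coefficient near zero, and which time-point contrast the 20% refers to, may be settled in an analysis plan that is not shown. Their absence here is not pressed.

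**Conclusion.** The point holds as one of efficiency and pre-specification. The article states the rule outright, so this is not detail left to another document. As written, the rule almost never keeps the six minimisation factors at the planned effect, and it makes the adjustment set a function of the observed effect and of the outcome. The expected cost at the planned effect is about 1-2 power points for residual R² of 5-10% and about 5 points at 20%, with standard errors that tend to be too large. Larger losses need a larger residual R², for which the article gives no evidence.

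The power figures rest on the physical activity design values, random dropout, deterministic minimisation and assumed factor prevalences. The mechanism needs only that the factors are balanced and that the threshold is relative to the estimate.

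**What to change.** For the primary analysis, replace forwards and backwards selection and the 20% rule with a model fixed before outcome data are analysed by group. For each outcome, include group, time, group by time, the baseline value of that outcome and the minimisation factors.

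State the exceptions in advance so that nothing enters twice. For HbA1c, the continuous baseline value replaces the HbA1c category. For weight and for activity, specify how redundant entry of BMI and of activity level alongside the baseline value is avoided. Other baseline characteristics, and any data-driven selection, move to a labelled sensitivity analysis.

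The cost is a change of wording and at most about eight degrees of freedom (five two-level factors use 5 and the four-level factor uses 3), fewer where a baseline value replaces a factor. No new data are needed, since all six factors are recorded before allocation.
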